## Abstract

**Background:**

Lung resection is the *gold standard* and the most effective curative treatment for lung cancer, especially in early-stage non-small cell lung cancer, improving long-term survival and quality of life. The growing body of evidence from randomized controlled trials supports the efficacy of prehabilitation in reducing both the incidence and severity of postoperative pulmonary complications and shortening the length of hospital stay.

**Objective:**

The general objective is to compare the effects of a single education session with different prehabilitation programs in patients undergoing lung resection surgery.

**Methods:**

Two hundred lung cancer patients who are going to be submitted to a lung resection surgery will be randomized into: (1) Inspiratory Muscle Training Group (n = 50), Expiratory Muscle Training Group (n = 50), Global Exercise Training Group (n = 50), and Control Group (n = 50). All patients will receive a single session in-person education session and written information regarding healthy habits to follow before, during, and after hospital discharge, and those from the IMT-G, EMT-G, and GET-G will start their 2-week prehabilitation interventions at ULS São João. Patients will be evaluated at baseline, after completing the prehabilitation program (post-intervention assessment), and 30 days post-discharge (follow-up assessment).

**Discussion:**

Despite diverse intervention strategies, prehabilitation consistently proves effective in bolstering patients' functional capacity. It may also help strengthen the respiratory muscles, which in turn affect lung function and cough effectiveness after thoracic surgery. This randomized trial has been designed to compare different prehabilitation programs and analyze their inherent costs.

## Introduction

1

Lung cancer is the leading cause of cancer death globally, [1]. In 2022, it accounted for roughly 12.4% of all cancer diagnoses and 18.7% of all cancer-related deaths [2].

Lung resection is the *gold standard* and the most effective treatment for lung cancer, especially in early-stage non-small cell lung cancer (NSCLC), improving long-term survival and quality of life [3]. However, only 15-20% of patients diagnosed with lung cancer are eligible for lung resection [3].

Although the well-known benefits of lung resection, it carries a considerable risk of postoperative pulmonary complications (PPC) occurrence, which negatively impact patients' morbidity and mortality, and escalate hospital costs [4,5]. Previous evidence has suggested that patients with superior functional capacity are better prepared to cope with the stress induced by surgery and, thus, less susceptible to PPCs [6]. The growing body of evidence from randomized controlled trials supports the efficacy of prehabilitation in reducing both the incidence and severity of PPCs and shortening the length of hospital stay (LOS) [[7], [8], [9]].

Prehabilitation lasts the time gap between the decision to proceed with surgery and the surgery. It aims to improve patients’ functional capacity by implementing a multimodal approach that includes medical optimization, physical exercise, nutritional and psychological support [6]. The guidelines for the enhancement of recovery after lung surgery highlight that the preoperative phase should consist of education and counselling, preoperative nutrition, smoking cessation (at least 4 weeks before surgery), alcohol dependency management, anaemia management, and pulmonary rehabilitation and prehabilitation [10].

A meta-analysis encompassing randomized controlled trials showed that patients receiving exercise prehabilitation programs had a lower odds ratio of PPCs (0.31; CI95%: 0.20; 0.48; I^2^ = 0%) and LOS (−3.02; CI95%: −4.82; −1.22; I^2^ = 85%), in comparison with patients who did not receive any intervention [11].

Although there are benefits of prehabilitation on PPCs and LOS, there is a considerable heterogeneity regarding modality, duration, and frequency, making decision-making for health professionals who are in charge of selecting the most successful approach for each patient. While some programs include inspiratory muscle training combined with aerobic exercises, others make different choices, encompassing resistance exercises, educational classes, and incentive spirometry, among many other options [11,12].

The rationale for expiratory muscle training in this study is based on the critical role of these muscles in coughing, airway clearance, and postoperative recovery. Since cough efficacy depends on vigorous expiratory muscle contraction, its impairment directly contributes to PPC [13]. Our previous research showed that patients with lower maximal expiratory pressure (MEP) have an increased risk of PPC (OR 7.44; 95% CI 1.23–19.47) [14]. Furthermore, peak expiratory flow (PEF) is a critical marker of impaired mucociliary clearance, establishing a strong scientific rationale for investigating targeted expiratory muscle training (EMT) as a distinct prehabilitation modality [15].

Based on the existing research gaps, we have designed the Fit4LungNeo project to investigate the effects of different prehabilitation programs in lung cancer patients.

The general objective of this project is to compare the effects of a single education session with different prehabilitation programs in patients undergoing lung resection surgery. Primary objective is to investigate prehabilitation's effectiveness in reducing postoperative pulmonary complications after 30 days of hospital discharge and length of hospital stay, in patients selected for lung cancer resections.

Secondary objectives: i) observe and compare the effect of prehabilitation on pulmonary function, respiratory muscle function, functional capacity, and physical fitness in patients undergoing lung resection surgery; ii) determine the impact of prehabilitation programs on patient-reported outcomes measures (PROMs), including fatigue, dyspnea, anxiety, depression, quality of life, and daily physical activity; iii) determine the cost-effectiveness of each prehabilitation program.

Our primary hypothesis is that all prehabilitation groups will experience a reduction in PPC and LOS, and better functional recovery postoperatively, compared to the usual care control group.

## Material and methods

2

### Design and ethics

2.1

The study design and protocol adhere to the Standard Protocol Items: Recommendations for Interventional Trials (SPIRIT) guidelines [16]. Any significant changes to the protocol will be reported to the trial registry and the Ethical Committee. Participation in this study is voluntary and without financial compensation.

Fit4LungNeo is a single-centered, controlled, randomized trial (RCT) with four parallel groups. Two hundred lung cancer patients who are going to be submitted to a lung resection surgery will be randomized into: (1) Inspiratory Muscle Training Group (IMT-G; n = 50), (2) Expiratory Muscle Training Group (EMT-G; n = 50), (3) Global Exercise Training Group (GET-G; n = 50), and (4) Control Group (CG; n = 50).

The study will be conducted by a multidisciplinary team and implemented at the Unidade Local de Saúde de São João (ULS São João) and the Faculty of Sport of the University of Porto (FADEUP) in Portugal.

The Fit4LungNeo was approved by the Ethical Committee from the ULS São João (52/2024) and registered on Clinicaltrials.gov (NCT06802627). All procedures will follow the principles of the Declaration of Helsinki. As it is mandatory in Portugal, civil liability insurance for clinical trials was taken.

### Recruitment and screening

2.2

The pulmonologist or thoracic surgeon will screen patients for eligibility at the first preoperative appointment at the Cardiothoracic and Pulmonology Departments of the ULS São João. After signing the informed consent, patients will be randomly allocated into one of the four study groups. Those who agree will start the initial assessment and be scheduled for the 2nd assessment day. Recruitment started in June 2025. The inclusion criteria are i. Patients ≥18 years old; ii. diagnosis of lung cancer; ii. Candidates for surgical treatment at the Cardiothoracic Surgery Service of USL São João. The exclusion criteria are i. diagnosis of cardiac or neurological disease, pulmonary hypertension, and renal failure; ii. Previous thoracic surgery; ii. Pneumonectomy; iv. Clinical cognitive and mental disorders; and v. Inability to walk independently; v. Emergency thoracic surgery procedures; vi. Participation in alternative prehabilitation programs.

During the study enrollment phase, we will track the total number of patients screened for eligibility, the number of patients excluded (with reasons for exclusion specified), and the final number of participants randomized [17]. We will report the number of participants who discontinue the intervention, are lost to follow-up, and are included in the intention-to-treat and per-protocol analyses (with reasons).

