### Blinding

2.4

Blinding participants and researchers will not be possible due to the nature of the interventions, except for the researchers responsible for the functional assessment.

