### Interventions

2.5

Regardless of the group allocation, patients will start the intervention one week after the baseline evaluation.

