**Fig. 1 fig1:**
[figure not shown]
Study design and timeline Flowchart of study procedures. IMT: Inspiratory Muscle Training; EMT: Expiratory Muscle Training; GET: Global Exercise Training Group.

In brief, on the first day of assessments, a physician will screen for eligibility criteria and forward the eligible patients to a physiotherapist and a nutritionist, who will collect data on anthropometry, body composition, sociodemographic, clinical history, and behavioral risk factors. Thereafter, questionnaires regarding PROMs will be applied in the form of interviews. Finally, patients will be provided with an accelerometer to measure daily physical activity during waking hours until the completion of the prehabilitation program.

Patients will be evaluated for pulmonary function, respiratory muscle function, functional capacity, and physical fitness on the second assessment day.

Afterward, all patients will receive an education class and written information regarding healthy habits to follow before, during, and after hospital discharge, and those from the IMT-G, EMT-G, and GET-G will start their 2-week prehabilitation interventions at ULS São João. The study design and timeline are presented in Fig. 1.

After the prehabilitation programs, all patients will be reassessed using the same baseline procedures and then undergo the surgery. The surgical team will register information on ASA classification, ARISCAT score, minimum oxygen saturation, surgical approach, total surgical time, and extent of resection. After surgery, all patients will receive standard care, including daily medical assessment, physiotherapy care, and analgesic protocol.

PPC and other complications and LOS will be documented based on the patient's medical record. Any postoperative complications and hospital readmissions within the following 30 days will also be monitored and recorded.

After hospital discharge, patients will be referred to outpatient physiotherapy and nursing care. Three weeks post-discharge, patients will attend a medical appointment and will be scheduled for the follow-up assessment. Participants will receive an accelerometer to wear for one week. Upon completion of data collection, a cost-effectiveness analysis will be conducted to determine the actual economic cost-benefit of each protocol.

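### Patients are allocated before the two baseline assessment days, so self-report, effort-dependent and activity baselines may be recorded in patients who already know their arm

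*Protocol article*

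**What the plan says.** Section 2.2 (Recruitment and screening) starts with eligibility screening at the first preoperative appointment and continues: "After signing the informed consent, patients will be randomly allocated into one of the four study groups". The next sentence is: "Those who agree will start the initial assessment and be scheduled for the 2nd assessment day". Baseline therefore follows allocation.

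Section 2.6 (Evaluation moments, text with Fig. 1) describes the two baseline days. On day 1, "questionnaires regarding PROMs will be applied in the form of interviews", and the accelerometer is handed out. For day 2: "Patients will be evaluated for pulmonary function, respiratory muscle function, functional capacity, and physical fitness on the second assessment day". Section 2.11.4 describes a 7-day accelerometer record at the start of the study.

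Section 2.4 (Blinding) says "Blinding participants and researchers will not be possible due to the nature of the interventions", "except for the researchers responsible for the functional assessment". Section 2.5 (Interventions) says that, in every arm, "patients will start the intervention one week after the baseline evaluation".

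Section 2.11 has all secondary outcomes measured at baseline, post-intervention and follow-up, apart from cost-effectiveness. Section 2.11.2 evaluates functional capacity and fitness through changes.

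**The concern.** A baseline value serves as a reference for later measurements because the arm cannot have influenced it. That holds by design only if it is recorded before the patient can know the arm. Here the stated order puts allocation first, and the patients are not blinded.

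Most of the exposed measurements depend on the patient. Questionnaire answers are self-report. The 6-minute walk, maximal inspiratory and expiratory pressures and grip strength depend on effort, and activity over a week is behaviour. A patient who has just learned that training is coming, or that only an education session is coming, may answer, try or move differently. If so, the arms differ at baseline for a reason that is not chance, and any analysis that subtracts or adjusts for baseline carries that difference into the estimated effect. The direction is not predictable: an inflated baseline in the trained arms understates benefit, and a depressed one overstates it.

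A second consequence is that a patient who leaves on learning the arm leaves no baseline data. The arms differ in burden (one education session, or that plus 6 or 10 supervised sessions under section 2.7), so such losses need not be balanced.

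**Working it through.** The article gives no figure on this point, so the check is of sequence first and of possible size second.

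**Sequence**

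| Step | Section | Position relative to allocation |
|---|---|---|
| Screening at first preoperative appointment | 2.2 | Before |
| Consent | 2.2 | Before |
| Random allocation | 2.2 | – |
| Day 1: interview questionnaires, accelerometer hand-out | 2.2, 2.6 | After |
| Day 2: lung function, respiratory muscle, functional and fitness tests | 2.2, 2.6 | After |
| 7-day baseline accelerometry | 2.6, 2.11.4 | After |
| Start of intervention, one week after baseline | 2.5 | After |

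Sections 2.5 and 2.6 put the start of the intervention after baseline, but they do not move the allocation. Section 2.3 (Randomization) describes how random numbers are drawn and sorted, and does not set the time of release. No section places randomisation after baseline or conceals the arm until baseline is done.

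**Who is blinded.** The exception in section 2.4 covers functional assessors. It does not name those who conduct the questionnaire interviews. A blinded assessor cannot favour an arm when measuring, but the patient's own effort and answers remain open to influence.

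**Possible size (illustration).** Let *b* be the between-arm shift in measured baseline, in SD units, caused by knowing the arm. Let *r* be the within-arm correlation of baseline with follow-up, and let δ be the between-arm difference at follow-up as it would be measured under either order, since patients know their arm by then in any case. Take equal SDs at both times and a shift that leaves *r* unchanged.

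- Change score: expected contrast = δ − *b*, so the bias is *b* in size.
- Baseline-adjusted (ANCOVA): the slope on baseline is *r*, so expected contrast = δ − *r*·*b*, and the bias is *r*·*b* in size.
- Unadjusted comparison of follow-up values: no bias from this source.

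The article gives neither *b* nor *r*; both are assumptions.

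| *b* (SD) | Change score | ANCOVA, *r* = 0.5 | ANCOVA, *r* = 0.7 |
|---|---|---|---|
| 0.1 | 0.10 | 0.5 × 0.1 = 0.05 | 0.7 × 0.1 = 0.07 |
| 0.2 | 0.20 | 0.5 × 0.2 = 0.10 | 0.7 × 0.2 = 0.14 |
| 0.3 | 0.30 | 0.5 × 0.3 = 0.15 | 0.7 × 0.3 = 0.21 |

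For a measurement completed before allocation is generated or released, *b* = 0 in expectation and this bias vanishes.

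**Primary outcomes.** Table 1 in section 2.9 marks pulmonary complications and length of stay at follow-up only. With no baseline value, the mechanism above cannot act on them.

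**The case against.** The strongest reply is that allocation is not disclosure. The article does not say when patients are told their arm, and Fig. 1, which shows the timeline, is not available in the text reviewed. Site staff may already hold the allocation back until both baseline days are done. This stands as a limit: the documents support that patients may know their arm at baseline, not that they do. It does not remove the point, because the written order permits disclosure before baseline and nothing forbids it.

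It is also fair that functional assessors are blinded, and that section 3.1 relies on standardised procedures and independent evaluators to offset the lack of blinding. That limits assessor bias on day 2. It does not reach self-report, patient effort or free-living activity.

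A reader might go further in three ways that the documents do not support:

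- **That eligibility is checked after allocation**, because section 2.6 says that "on the first day of assessments, a physician will screen for eligibility criteria". Section 2.2 already places screening before consent, and the two sections agree if screening, consent, allocation and day 1 fall on one visit. This is not a contradiction.
- **That the opening words of "Those who agree will start the initial assessment and be scheduled for the 2nd assessment day" show patients accepting or refusing their arm.** They may simply mean agreement to take part. The order of allocation and baseline does not depend on that reading.
- **That patients who leave early fall out of the intention-to-treat set.** Intention-to-treat keeps everyone randomised. Section 2.2 commits to reporting numbers randomised, losses and inclusion in each analysis with reasons, and section 2.6 takes complications and length of stay from the medical record, so these may remain obtainable. What is lost for such patients is the baseline data.

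**Conclusion.** The point holds in this form: as written, the plan allocates unblinded patients before both baseline days and does not withhold the allocation, so baseline questionnaires, effort-dependent tests and accelerometry may be recorded with the arm known. The comparisons exposed are those of secondary outcomes, other than cost-effectiveness, that use change from baseline or adjust for it. Changes are stated for functional capacity and fitness; the article names no model for the rest.

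The size is unknown. Under the assumed ranges, the bias is 0.1 to 0.3 SD for change scores and 0.05 to 0.21 SD for baseline-adjusted estimates, in either direction, and it is nil if patients are in practice not told until baseline is complete. The primary outcomes are affected only if outcomes are not obtained for patients who leave on learning their arm. The number of such patients cannot be estimated from the article. This is an inexpensive improvement to make, not a flaw that undermines the primary comparison.

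**What to change.** Rewrite the order in section 2.2 so that, for patients enrolled from now on, eligibility is confirmed, consent is signed and both baseline assessment days are completed before the allocation is generated or released to the patient and the treating team. Report the change to the registry and the Ethics Committee, as section 2.1 requires for significant changes. If the site already withholds the arm until baseline is complete, it is enough to say so in section 2.2.

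The cost is small. No visit or measurement is added, and training sessions are booked within the one-week gap that section 2.5 already provides. Two limits should be accepted openly:

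- Recruitment began in June 2025, so patients already enrolled under the current order will have been assessed differently. The date of the switch should be recorded.
- The 7-day accelerometer record may run past the second assessment day, so its later days could still follow disclosure. Holding the arm back until that record ends would use up the booking gap and is not proposed.

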### Randomization

2.3

Patient randomization was conducted in Microsoft® Excel, where a list of participants will be generated and the RAND function will be applied to create a column of random numbers. Sorting this column will allow for the random allocation of patients to different study groups.

### Blinding

2.4

Blinding participants and researchers will not be possible due to the nature of the interventions, except for the researchers responsible for the functional assessment.

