### Primary outcomes

2.10

PPC (from surgery to 30 days after discharge) will be screened according to the joint agreement and standardized definitions provided by the European Society of Thoracic Surgery (ESTS) and the Society of Thoracic Surgeons (STS) [20].

LOS and readmissions (from surgery to 30 days after discharge) will be based on the number of postoperative hospitalization days, including hospital readmissions related to surgery, assessed in clinical data. For those patients with persistent air leak, allowed to return home with a drainage tube, it be resisted the number of days util remove the tube.

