#### Functional capacity and physical fitness

2.11.2

Functional capacity and physical fitness will be evaluated through changes in aerobic endurance, lower body strength, handgrip strength, balance, speed walk, lower body power, agility, coordination, and dynamic balance, as described below.

Aerobic endurance will be assessed by the 6-min walk test (6-MWT), according to the American Thoracic Society (ATS) guidelines [23]. Distance (in meters), maximum and minimum oxygen saturation (%), and maximum and minimum heart rate (bpm) will be recorded. Both oxygen saturation and heart rate will be collected using the Spirodoc® (Rome, Italy).

Lower body strength changes will be measured using the sit-to-stand test of the Senior Fitness Test [24]. Handgrip strength will be assessed using the dynamometer Jamar Plus + Digital hand dynamometer (Sammons Preston Inc., Bolingbrook, Illinois, USA). Measurements will be carried out according to the American Society of Hand Therapists’ Recommendations [25].

The Short Physical Performance Battery (SPPB) will be used to assess balance, walking speed, and lower body power [26,27]. Agility, coordination, and dynamic balance will be measured by the timed up and go test (TUG) [28].

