### Strengths and limitations

3.1

This study possesses several notable strengths that enhance the reliability and validity of its findings. Firstly, the RCT design ensures rigorous participant allocation, minimizing selection bias and bolstering the validity of causal inferences. Secondly, the comprehensive assessment of functional capacity provides a holistic view of patient health. Thirdly, including PROMs, captures the patient's subjective experience, providing a well-rounded understanding of the intervention's impact. Fourthly, monitoring heart rate and oxygen saturation during exercise sessions allows for detailed adherence and physiological response analysis. Fifthly, the standardized pre- and post-operative care protocols and controlled warm-up, cool-down, and exercise program duration strengthen the attribution of observed effects to the exercise intervention. The study's mechanistic approach offers insights into how lifestyle and daily habit changes influence patient health and whether the intervention is sufficient to elicit positive post-operative changes. Finally, this study addresses a clinically relevant question, specifically evaluating the comparative effectiveness of different prehabilitation modalities and identifying potential superior interventions.

The study has some limitations that need to be considered. Although it may influence the results, including patients in neoadjuvant therapy will be controlled by statistical analysis. Risk stratification, in turn, will be used as an analysis variable, and not as an exclusion criterion. The inclusion of only individuals without heart disease, although it may limit the number of participants, aims to isolate the effect of the intervention on pulmonary complications, minimizing the influence of comorbidities. The relatively short duration of the intervention (2 weeks), although it may be sufficient for physiological changes, may not be ideal for long-term adaptations. However, it is important to remember that this period was defined so there would be no delays in the patient's surgery. The absence of blinding, justified by the nature of the intervention, will be mitigated by standardizing procedures and using independent evaluators. These limitations, however, are balanced by the strengths of the study.

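### Blinding stops at the functional assessors, so by the protocol's own rule PPC coding and the attribution of readmissions to surgery are left unmasked, although both are chart-based and could be masked

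*Protocol article*

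**What the plan says.** Section 2.4 (Blinding) gives a general rule with one exception: "Blinding participants and researchers will not be possible due to the nature of the interventions, except for the researchers responsible for the functional assessment".

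Section 2.11.2 shows what functional assessment means here: "Functional capacity and physical fitness will be evaluated through changes in aerobic endurance, lower body strength, handgrip strength, balance, speed walk", and so on through a list of performance tests. Table 1 classes all of these as secondary.

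The primary outcomes are PPC and LOS. On their source, section 2.6 says "PPC and other complications and LOS will be documented based on the" patient's medical record. Section 2.10 says that PPC "will be screened according to the joint agreement and standardized definitions provided by" the European and American thoracic surgery societies (ESTS and STS), and that LOS rests on the "number of postoperative hospitalization days, including hospital readmissions related to surgery, assessed in clinical data". Neither section names the person who codes these items or says whether that person is masked.

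For patient-reported outcomes (PROMs), section 2.6 says that "questionnaires regarding PROMs will be applied in the form of interviews". The interviewer is not identified.

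Two statements bear on mitigation. Section 3.1 says that the absence of blinding "will be mitigated by standardizing procedures and using independent evaluators". Section 2.15 says that a research team member will verify the collected data twice.

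**The concern.** The masking is placed where it matters less. The one masked group measures secondary outcomes, while the primary outcomes fall under the unblinded rule.

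Two steps in the primary outcomes need judgement. Someone must read a chart and decide whether an event meets a PPC definition. Someone must also decide whether a readmission is attributable to the operation, because only then do its days count towards LOS. The primary hypothesis in the Introduction is that every prehabilitation group will have fewer PPCs and a shorter stay than control. If the coder knows the arm, the likely direction of any coding error is therefore known in advance, and it favours the hypothesis.

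The protocol justifies non-blinding by the nature of the interventions. That explains why patients and therapists cannot be blinded. It does not explain why a later reading of the record should be unmasked.

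**Working it through.** **Step 1: the text side by side.** The protocol gives no figure for this point, so the check is mainly a comparison of sections.

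| Item | Outcome level | Source | Covered by the section 2.4 exception? | Judgement needed |
|---|---|---|---|---|
| 6-minute walk, sit-to-stand, handgrip, SPPB, TUG | Secondary | Direct test | Yes | Limited |
| PPC | Primary | Medical record, ESTS/STS definitions | No | Yes, narrowed by the definitions |
| LOS, index stay | Primary | Clinical data | No | Little; it is a count of days |
| LOS, readmission days | Primary | Clinical data | No | Yes; relation to surgery |
| PROMs | Secondary | Interview | No | Patient's answer, plus interviewer influence |

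Even if the exception is read widely, to include the pulmonary and respiratory muscle tests done on the same assessment day, it still covers only secondary outcomes.

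**Step 2: does section 3.1 close the gap?** There are two readings. The independent evaluators may be the functional assessors of section 2.4, who do not cover the primary outcomes. Or they may be other people, in which case section 2.4 implies that they are not masked. Independence from delivery is not the same as masking. Neither reading gives masked PPC coding.

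**Step 3: how large could the bias be?** The document gives no PPC rate and no coding error rate, so everything below is assumed. Take a true PPC rate p that is equal in both arms, complete recording in control, and a fraction m of events missed in one exercise arm. The coded rates are p and p(1 − m), so the apparent risk ratio is 1 − m although the true one is 1.

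The normal-approximation rejection probability of a two-sided 5% test with n per arm uses

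- d = p − p(1 − m)
- se0 = √(2·p̄(1 − p̄)/n), where p̄ is the mean of the two coded rates
- se1 = √((p1(1 − p1) + p2(1 − p2))/n), where p1 and p2 are the two coded rates
- P(reject) = 1 − Φ((1.96·se0 − d)/se1) + Φ((−1.96·se0 − d)/se1)

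Example with n = 50, p = 0.30, m = 0.20: coded rates 0.30 and 0.24, d = 0.06, p̄ = 0.27, se0 = 0.0888, se1 = 0.0886. P(reject) = 1 − Φ(1.287) + Φ(−2.642) = 0.099 + 0.004 = 0.103.

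| True PPC rate (both arms) | 10% missed | 20% missed | 30% missed |
|---|---|---|---|
| 20% | 5.7% | 8.1% | 12.5% |
| 30% | 6.3% | 10.3% | 17.7% |
| 40% | 6.9% | 13.2% | 24.3% |

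**Step 4: sensitivity to the assumptions.** Take p = 25%, 45 per arm and an exact calculation for the chi-square test. Without bias the test rejects 5.4% of the time. Under-recording alone gives 6.3% (10% missed) and 9.3% (20% missed). Now add an opposite error in control, with 5% of non-events over-called and 20% of exercise-arm events missed. The coded rates become 0.25 + 0.75 × 0.05 = 0.2875 and 0.25 × 0.8 = 0.20, the risk ratio is 0.20/0.2875 = 0.70, and rejection is 16.9%. With a continuity correction the same case gives 10.6%. The milder pair (3% and 10%) gives a risk ratio of 0.83 and 8.6%, or 4.8% with the correction. The direction is the same throughout; the size follows from what is assumed.

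**The case against.** The strongest reply is that section 2.4 never mentions PPC coders, readmission judgements or interviewers. It is one sentence in a condensed article, and no role is named for coding. This stands as far as it goes: a reader might infer that the protocol explicitly has these outcomes judged by staff who know the arm, and it does not say that. The narrower statement survives. The sentence is a general rule with a single exception, and these steps lie outside the exception. That is a stated design choice, not merely a detail left to a fuller document.

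Second, safeguards exist. The ESTS/STS definitions limit discretion, data are verified twice, postoperative care is standard for all arms, and section 3.1 lists the absence of blinding as a limitation. These reduce the scope for error. None of them is masking, and a second check by someone who also knows the arm can share the same lean.

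Third, a reader might infer that the whole of both primary outcomes is exposed to coder judgement. That is too strong. LOS is mostly a count of days from the record, and only the attribution of readmissions depends on the coder.

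Fourth, a reader might take a false-positive rate near 17% as the effect. It needs two opposing errors at once, at assumed rates, with an uncorrected test that the article does not specify. The document does not support it as an estimate.

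Fifth, on PROMs, a physiotherapist and a nutritionist collect first-day data, and the same professions deliver the education. The document does not say that they are the same individuals or that they conduct the interviews. Patients know their arm in any case.

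**Conclusion.** The point holds in a limited form. By the rule in section 2.4, PPC coding and the surgery-relatedness of readmissions are left unmasked, for a reason that does not apply to a chart-based step. Section 3.1 does not resolve this, and the two sections need to be aligned.

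The size of any bias cannot be derived from the document. With under-recording in one exercise arm as the only error, assumed PPC rates of 20% to 40% and 10% to 30% of events missed, the rejection rate under no effect runs from about 6% to 24%. These figures show what is possible; they do not predict what will happen. PPC is the main exposure, readmission days in LOS a smaller one, and index-stay days are little affected. The PROM interviews are a side issue.

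This is a cheap improvement to the primary comparison. It does not show that the trial's results will be biased.

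**What to change.** Amend sections 2.4 and 2.10 to state that PPC, by the ESTS/STS definitions, and the surgery-relatedness of each readmission are coded from record extracts with allocation and prehabilitation notes removed. The coder should be an existing team member who takes no part in delivering the programmes and does not know the arm. Apply this also to patients already enrolled, since recruitment began in June 2025 and charts can be coded retrospectively. Reword section 3.1 to say who the independent evaluators are, whether they are masked and which outcomes they cover.

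Keep the current LOS definition. Counting all-cause readmission days would redefine a primary outcome after recruitment began, and masked attribution is enough.

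As a side note, have PROM interviews done by staff masked to arm where existing staffing allows. This removes only the interviewer's part of the bias.

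The cost is a short amendment and some time to redact records. Masking the coder cannot remove bias already present in notes written by clinicians who know the arm, and this should be stated as a remaining limitation.
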